#### Social Cohesion

Social cohesion will be measured using items adapted from Sampson et al [49]. The adapted measure consists of 5 questions asking respondents to rate neighborhood’s perceived closeness of residents, willingness to help, trust, conflict, and values. The 5 items are each scored on a 5-point Likert scale ranging from “strongly agree” to “strongly disagree” [49]. Total scores range from 5 to 25, with higher scores representing a higher sense of community.

#### Help-Seeking

The help-seeking intention will be measured using 2 adapted items from the CBDMHI developers [30] that ask respondents “Would you be comfortable seeking help from others if you were experiencing sadness, stress or burnout?” and “Would you be comfortable seeking help from others if you needed something to prepare for or in the aftermath of a disaster?” Response options are scored on a 4-point scale ranging from “I would not be comfortable at all” to “I would be very comfortable.” Total scores range from 2 to 8, with higher scores representing higher help-seeking intention.

#### Coping

Coping will be measured using an adapted version of the Brief-Coping Orientation to Problems Experienced Inventory (Brief-COPE) [50]. The adapted coping measure consists of 4 questions targeting acceptance, denial, self-distraction, and solution-focused coping. Items are scored on a 5-point Likert scale ranging from “None of the time” to “All of the time.” Higher scores represent higher engagement in a given coping style, and are, therefore, evaluated as individual items.

#### Psychological Preparedness

Psychological preparedness will be measured using the Psychological Preparedness for Disaster Threat Scale (PPDTS) [51]. The PPDTS is a self-report questionnaire that consists of 18 items, each scored on a 4-point Likert scale ranging from “not at all true of me” to “exactly true of me” [51]. Higher scores represent higher perceived psychological preparedness [51].

### Planned Data Analysis

Descriptive statistics will be provided for demographic data. Phase 1 community consultation interview data will be analyzed using thematic analysis [52] to explore participants’ physical, psychological, social, and environmental needs following the 2019-2020 bushfires. Inductive thematic analysis has been selected for this study as it is a useful qualitative approach for applied research designs [53]. Thematic analysis provides a flexible yet robust, systematic framework for coding data and has been used widely in the health sciences [53]. Data analysis will involve an iterative process including familiarizing oneself with the data, generating initial codes, searching for themes, reviewing themes, defining and naming themes, and producing the report [52,54].

One-way repeated measures ANOVAs will be performed for phase 3 outcome measures to identify any changes in pre- and postintervention outcomes, and whether those changes were maintained up to 6 weeks. Multilevel mixed models nested in time may also be used, as these analyses are more robust to missing data and can be used to model change trajectories over time. Where a change in score across time points is identified, the reliable change index will be used to assess the clinical significance of this change to provide further insight into the clinical meaningfulness and use of the program.

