### Proposed Sample

The proposed sample for phase 1 will be determined through informational power [38]. Informational power is based on 5 concepts, aim, specificity, theory, dialogue, and analysis. When informational power is met the sample size will be determined.

The proposed sample for phase 3 is up to 20 participants, which is estimated as more than 15% of the total population of the target community. This target sample size is based on previous adaptations of the CBDMHI that used no more than 20 participants per intervention group [30,42]. This number is also in line with the recommended treatment group size for pilot studies [45].

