#### Acceptability

Acceptability of the intervention will be measured using Likert-style and open-ended questions. The Likert-style questions will be scored using a 5-point Likert scale ranging from “strongly disagree” to “strongly agree,” with higher scores indicating higher acceptability. Open-ended questions (eg, “what did you like about the workshop?”) will also be used to measure acceptability. Participants will also be invited to take part in an optional follow-up semistructured interview to assess acceptability and perceived unhelpfulness.

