## Results

Data collection commenced following support from the Black Summer Recovery Grant Scheme. As of January 2023, more than 10% of the identified rural community in the Northern Tablelands has participated in phase 1 interviews. These interviews have been transcribed and a thematic analysis of the data is currently taking place. As of September 2023, a total of 10 rural community members participated in the phase 3 intervention. Follow-up data were collected in November 2023, and the first results are to be submitted for publication in 2024.

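### The reliable change index is computed only after a group-level change is found and is read as clinical significance, which it does not measure

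*Protocol article*

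**What the plan says.** Phase 3 is an uncontrolled pre, post and 6-week design. Planned Data Analysis states: "One-way repeated measures ANOVAs will be performed for phase 3 outcome measures to identify any changes in pre- and postintervention outcomes". Mixed models are mentioned as an option. The next step is conditional: "Where a change in score across time points is identified, the reliable change index will be used to assess the clinical significance" of the change, and the stated purpose is "to provide further insight into the clinical meaningfulness and use of the program".

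On numbers, Proposed Sample says "The proposed sample for phase 3 is up to 20 participants", and Results reports that "a total of 10 rural community members participated in the phase 3 intervention" as of September 2023.

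The Psychological Distress section describes the two ends of the K10 range, and the Resilience section prints bands for the BRS. Neither is linked to the RCI. The Coping section says that higher scores mean more use of a given coping style and that they "are, therefore, evaluated as individual items".

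**The concern.** Two things are wrong with the rule as stated.

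First, the condition. The RCI is calculated person by person, and its use is in showing who changed when the average does not. Making it wait for a change in the mean removes that use. It is not calculated when some people improve and others worsen by similar amounts. It is also not calculated when about 10 participants give too little power to detect a mean change.

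Second, the label. Exceeding measurement error is a statement about precision. Whether the change matters clinically needs a separate criterion, such as crossing a recognised score boundary, and the plan ties none to the RCI.

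At stake is the reading of preliminary effectiveness in a bushfire-exposed community, where results are meant to inform scale-up. A count of people who reliably worsened is a natural quantitative warning sign in a study without a control group. Under the stated rule it may never be produced.

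**Working it through.** The article gives no alpha, SD, reliability or RCI threshold, so there is no figure of its own to reproduce. All such values below are assumptions.

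**1. What the threshold contains.** Threshold = 1.96 × SD × √(2(1 − r)), where r is the reliability. In baseline SD units:

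- r = 0.7: 1.52
- r = 0.8: 1.24
- r = 0.9: 0.88

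For the K10 with an assumed SD of 8:

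- r = 0.90: 1.96 × 8 × √0.20 = 7.0 points
- r = 0.85: 1.96 × 8 × √0.30 = 8.6 points

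Only SD and reliability enter. A more reliable scale gives a smaller threshold, whatever the clinical importance of the change.

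**2. A constructed example of a flat mean.** Two of 10 people worsen by 10 K10 points and eight improve by 2.5. Mean change = (2 × 10 − 8 × 2.5)/10 = 0. Both people who worsened exceed 8.6 points, but with no mean change identified the RCI is not run. This shows that the case is possible, not that it is likely.

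**3. How often the condition would block the calculation.** Simulation with 40,000 runs, three time points, one-way repeated measures ANOVA at alpha 0.05, and baseline SD 1. A share of participants truly worsen by 1 SD at both later time points and the same share improve by 1 SD. The RCI is taken from pre to post.

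| n | r | Share truly worse | ANOVA significant | Mean number flagged reliably worse | P(at least one flagged) |
|---|---|---|---|---|---|
| 10 | 0.8 | 20% | 0.007 | 0.85 | 0.638 |
| 10 | 0.8 | 30% | 0.003 | 1.16 | 0.758 |
| 10 | 0.9 | 20% | 0.001 | 1.36 | 0.868 |
| 10 | 0.9 | 30% | 0.000 | 1.92 | 0.945 |
| 20 | 0.8 | 20% | 0.007 | 1.71 | 0.873 |
| 20 | 0.8 | 30% | 0.003 | 2.31 | 0.938 |
| 20 | 0.9 | 20% | 0.001 | 2.74 | 0.982 |
| 20 | 0.9 | 30% | 0.000 | 3.85 | 0.997 |

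The last two columns are what an unconditional RCI would show. Under the plan almost none of it would be calculated. The offset is exact by construction.

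**4. Low power.** With a real uniform shift after baseline and r = 0.8, the ANOVA is significant with these probabilities:

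- 0.3 SD: 28% (n = 10), 55% (n = 20)
- 0.5 SD: 66% and 95%
- 0.8 SD: 97% and 100%

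Sample size therefore blocks the calculation mainly for small mean shifts.

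**5. Background of chance flags.** With no true change, each comparison is flagged as worse with probability 0.025. For one scale, P(at least one) = 1 − 0.975^10 = 0.22 for 10 people and 1 − 0.975^20 = 0.40 for 20. For four scales and 10 people there are 40 comparisons: 40 × 0.025 = 1.0 expected false deterioration, and, if independent, 1 − 0.975^40 = 0.64 for at least one.

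**The case against.** The sentence on the RCI does not contain the word group. That stands as a caveat, but the ANOVAs are the step meant to identify change. If any individual's change were enough, the condition would be almost empty.

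Nothing is destroyed: the K10 is still collected at three time points, and individual data could be shown. That also stands. The worsening is not calculated under the plan, which is different from being concealed.

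This is a small pilot aimed mainly at acceptability and feasibility, and no decision rule rests on the RCI. This limits the weight of the point.

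Readers might go further in four ways that the documents do not support:

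- *The rule selects favourable results.* The ANOVAs look for change in either direction and the RCI is two-sided. A worsening mean satisfies the condition as readily as an improving one. The rule favours outcomes that moved. The article also speaks of clinical significance and meaningfulness, not of benefit.
- *The plan will generate many chance improvements.* Taking 10 people, 9 outcomes and 2 contrasts gives 180 comparisons and 180 × 0.025 = 4.5. That describes an unconditional RCI. With no true change and alpha 0.05, about 9 × 0.05 = 0.45 outcomes would meet the condition, leaving about 0.45 × 20 = 9 comparisons.
- *Negative reactions are probed nowhere but in an optional interview.* Perceived unhelpfulness is named only with the "optional follow-up semistructured interview to assess acceptability and perceived unhelpfulness", but the Acceptability section also has agreement items and open-ended questions outside that interview.
- *The plan applies the RCI to single coping items and to the help-seeking score.* Coping is analysed item by item, and for help-seeking "The help-seeking intention will be measured using 2 adapted items", but the article does not list which measures receive an RCI. That may be left to an analysis plan not shown. An RCI can also use a test-retest coefficient, so a single item does not rule it out.

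**Conclusion.** The point holds in two parts. The article makes an individual-level statistic depend on a group-level result, and it interprets that statistic as clinical significance without any clinical criterion. Both follow from what the article states, not from detail it leaves out.

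Under exact offset, with the assumed reliabilities of 0.8 to 0.9 and true shifts of 1 SD in 20% or 30% each way, the condition is met in at most 0.7% of runs. An unconditional RCI would flag at least one worsened person in 64% to 95% of runs at n = 10 and in 87% to more than 99% at n = 20. These figures illustrate the mechanism; partial offset would meet the condition more often.

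The consequence is moderate. It touches the reading of preliminary effectiveness and possible harm in a small uncontrolled pilot. It does not touch the feasibility or acceptability aims. The change should be made, but nothing else in the study depends on it.

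**What to change.** Replace the conditional sentence with a rule along these lines:

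- Compute the RCI for every participant with paired data, whatever the ANOVA or mixed model shows, on the multi-item scales: K10, BRS, PPDTS, and social cohesion if its reliability is adequate. State the reliability coefficient, the SD and their source.
- Report, for each scale, the numbers reliably improved, unchanged and reliably deteriorated, and call this *reliable change*.
- Use *clinically significant* only where reliable change also crosses a published or prespecified cutoff. The article gives only the end points of the K10, so a category boundary would have to be cited. Follow-up was collected in November 2023, so a boundary chosen now should be an established one, with the date of choice stated.
- Leave out the single coping items unless a test-retest reliability is available. As an illustration with SD 1 and retest 0.4 to 0.6 (assumed), the threshold is 1.96 × √(2 × 0.6) = 2.15 down to 1.96 × √(2 × 0.4) = 1.75, on an item that spans only 4 points.

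The cost is a change of wording and one small table; no new data are needed. There are two drawbacks. Error alone flags about 2.5% of comparisons in each direction, about one false deterioration in 40 comparisons (10 people, four scales), so the expected count should be printed beside the observed one and the table read descriptively. Also, eligibility sets no distress threshold, so people with low K10 scores at baseline cannot improve across a cutoff, and the number who could should be given.

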**Figure 1 figure1:**
[figure not shown]
Study phases. CBDMHI: Community-Based Disaster Mental Health Intervention.

Phase 3 will involve piloting the adapted CBDMHI in the identified rural community. Phase 3 has been registered with the Australian New Zealand Clinical Trials Registry (ANZCTR) registration (ACTRN12623001023640). As part of this phase, the research team will train local and respected community leaders to administer or co-deliver the adapted CBDMHI. The intervention will consist of facilitated discussion, the space to share personal experiences, the establishment of peer support, the establishment of safety, and learning and practicing coping skills specifically for disaster-related distress. The intervention also provides practical training in disaster preparedness and response techniques that participants can use to support themselves and other community members during future hazards.

Phase 3 of the study will pilot the CBDMHI with residents of the affected community. The pilot intervention will use a pretest and posttest design to assess the acceptability of the intervention, as well as levels of psychological distress, resilience, coping, community cohesion, psychological preparedness, and help-seeking intentions following the intervention. Participants will complete measures before and after the workshop to assess the treatment effectiveness, as well as a 6-week follow-up. Due to the community setting and different availabilities of community members living in rural areas with property and farming obligations, random allocation is unlikely to be possible. Workshop participation and thus treatment implementation will, therefore, be a within-subject design with participants acting as their own controls. Drawing on the results from this study, a framework with Australian bushfire-specific materials will be developed and made available to facilitate broader implementation in the future to support recovery in other fire-affected Australian communities.

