### Outcomes

#### Measures

Participants in phase 3 of this research will complete a range of self-report measures prior to the intervention, at completion of the intervention, as well as a 6-week follow-up to assess durability. Measures will be collected via an anonymous survey completed in person with trained assessors pre- and postintervention and follow-up measures will be emailed along with reply paid envelopes. To link pre- and posttest questionnaire results, participants will be assigned a unique identifier.

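### The reliable change index is computed only where a group-level change is found, so opposing individual changes can go unexamined in a study of 10 people

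*Protocol article*

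**What the plan says.** Planned Data Analysis (protocol article) sets out the phase 3 analysis in three steps.

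- The main analysis is at group level: "One-way repeated measures ANOVAs will be performed for phase 3 outcome measures to identify any changes in pre- and postintervention outcomes". It also asks whether changes last to 6 weeks. Multilevel mixed models are named as an option.
- The reliable change index follows on a condition: "Where a change in score across time points is identified, the reliable change index will be used".
- Its stated purpose is "to assess the clinical significance of this change to provide further insight into the clinical meaningfulness and use of the program".

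No other section plans the index for all participants or all outcomes. Study Design describes "a within-subject design with participants acting as their own controls", so there is no comparison group. Proposed Sample states that "The proposed sample for phase 3 is up to 20 participants", and Results reports that "a total of 10 rural community members participated in the phase 3 intervention".

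**The concern.** The reliable change index asks whether one person's change is larger than measurement error would explain. Whether the group mean has moved does not answer that question. The ANOVA is there to identify changes, the index applies where a change is identified, and its purpose refers back to that same change. Read in sequence, the index depends on the group-level result.

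Two things follow. First, if some participants improve and others worsen, the mean may stay put and nobody's change is classified. Second, a group test on 10 people detects few modest effects. When there is a modest true benefit, the samples in which the test succeeds tend to be those that by chance contain many improvers and few who worsened.

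The workshop includes sharing personal disaster experiences, and the results are meant to inform wider use. Whether anyone reliably worsened is therefore worth knowing, whatever the mean does.

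**Working it through.** The protocol states no alpha, SD, reliability, cut-off or expected effect, so there is no figure of its own to reproduce.

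**Inputs from the protocol:** three time points (pre, post, 6 weeks); one-way repeated measures ANOVA; n = 10 actual, up to 20 planned; K10 scored so that higher means more distress.

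**Assumed inputs:** K10 SD 7; reliability 0.90; two-sided alpha 0.05; normally distributed true individual changes, held to follow-up, with SD from 0 to 7 points.

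**Cut-off.** 1.96 × SD × √(2 × (1 − reliability)) = 1.96 × 7 × √0.2 = 6.14 points.

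**1. Worsening with no index computed (mean change 0, n=10)**

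The error variance of a difference is 2 × 49 × 0.1 = 9.8, so the SD of observed change is √(9.8 + s²), where s is the true-change SD. One person crosses the worsening threshold with probability P(Z > 6.14/√(9.8 + s²)) = p. At least one of 10 does so with probability 1 − (1 − p)¹⁰. The last column is simulated and requires in addition that the ANOVA is not significant.

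| True-change SD | SD of observed change | p | At least one of 10 | At least one, index not run |
|---|---|---|---|---|
| 0 | 3.13 | 2.5% | 22% | 21% |
| 2 | 3.72 | 4.9% | 40% | 38% |
| 3.5 | 4.70 | 9.6% | 63% | 61% |
| 5 | 5.90 | 14.9% | 80% | 76% |
| 7 | 7.67 | 21.2% | 91% | 86% |

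The ANOVA is significant in about 5–8% of runs across these rows. The first row is measurement error alone, and some crossings in the other rows are too. Two or more people crossing with no index run is firmer evidence: about 22% of runs at SD 3.5 and 43–62% at SD 5–7.

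A limiting case in SD units, with reliability 0.8: exactly half the group gains 1.5 SD and half loses 1.5 SD. The cut-off is 1.96 × √0.4 = 1.24 SD and the error SD of a difference is √0.4 = 0.63. A person who truly gains is classed as improved with probability P(Z > (1.24 − 1.5)/0.63), about 66%, which is 33% of the group. By symmetry 33% are classed as worsened. The ANOVA was significant in 0% of simulated studies at n=10 and at n=20.

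**2. Shares seen only when the condition is met (mean benefit 2 points)**

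The unconditional shares are P(Z > (6.14 − 2)/SD of observed change) for improved and P(Z > (6.14 + 2)/SD of observed change) for worsened.

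- True-change SD 3.5: 4.14/4.70 = 0.88 gives 19% improved; 8.14/4.70 = 1.73 gives 4% worsened.
- True-change SD 7: 4.14/7.67 = 0.54 gives 29% improved; 8.14/7.67 = 1.06 gives 14% worsened.

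Among simulated n=10 studies with a significant ANOVA, 26–43% are classed as improved and 1–5% as worsened over the same range. At n=20 and SD 5–7 the figures are 30–38% and 5–8%.

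A separate simulation in SD units (reliability 0.8, true-change SD 0.5) shows the same pattern. At n=10 and a gain of 0.2 SD, improved rises from 9.8% to 15.5% and worsened falls from 3.7% to 0.8%.

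**3. Where the bias disappears**

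- Zero mean change, SD 7, n=10: improved 21.3% over all runs and 21.8% when the condition is met; worsened 21.2% and 21.7%.
- High power (n=20, gain 0.8 SD): improved 29.3% in both; worsened 0.6% and 0.5%.

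**The case against.** **The wording is not explicit.** The condition does not say significant, group-level or ANOVA, and an article may leave the exact trigger to a fuller plan. This lowers certainty a little. The group-level reading remains the natural one, and the sentence states a rule, so this is more than a missing detail. If each person's own change was meant, the sentence still needs correcting.

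**The bias in the shares is conditional.** A reader might infer that the plan always inflates the share improved and shrinks the share worsened. The documents do not support that. The ANOVA is non-directional, so at zero true effect there is no average bias, and a significant worsening would push the shares the other way. Nor does the protocol say that shares will be reported; it gives the index only the purpose of judging clinical significance. This objection stands and limits the second part of the point. It does not touch the first part, which needs no mean effect.

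**The size depends on assumed heterogeneity.** The protocol supplies none. The upper figures need true changes that vary nearly as much as baseline scores. This stands, and is why the full range is shown with its measurement-error floor.

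**The index is not the only way to notice harm.** A reader might infer that it is. The Acceptability section provides open-ended questions and an optional interview covering perceived unhelpfulness, and mixed models may describe trajectories. These do not classify each participant's change on the scales, and the interview is self-selected, but they exist.

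**The stakes are modest.** This is an uncontrolled pilot that acknowledges its small sample and the need for replication, and no decision rule rests on the index. That is a fair argument on severity.

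**Conclusion.** The point holds in a limited form. On its natural reading, the protocol makes an individual-level index depend on a group-mean finding, and nothing elsewhere in the document corrects this. With 10 participants and no mean change, someone crosses the worsening threshold with no index computed in about 38–86% of simulated studies for true-change SDs of 2–7 points, against 21% from measurement error alone. The overstated improvement and understated worsening are a further consequence only where the true mean benefit is modest and power is low.

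Every magnitude rests on the assumed SD, reliability, alpha and spread of true change. The cancelling of opposing changes in the mean needs none of those values. This is a should-fix matter: the rule is wrong as written, but it governs a secondary interpretive analysis in a pilot.

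**What to change.** Delete the condition. For the multi-item scales (K10, BRS, PPDTS), compute the index for every participant with a pre score and a later score, at post and at 6 weeks, whatever the ANOVA or mixed model shows. Report the numbers reliably improved, unchanged and worsened side by side for each scale and time point. State that some single crossings are expected from measurement error: at a 1.96 cut-off, 2.5% per person in each direction, or 10 × 0.025 = 0.25 of a person per direction among 10.

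The cost is one sentence in the plan and one small table. No new data are needed, because the protocol already links each participant's questionnaires by a unique identifier. The improvement rate may look less favourable than one reported only where the group test succeeds.
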